## 2. Materials and Methods

### 2.1. Overview of Study Procedures

Autistic participants (i.e., individuals who already have completed diagnostic assessments and/or have a documented and verified diagnosis) will be recruited from a clinical research database through collaboration with a local Children’s Hospital. Interested participants will be screened over the phone and/or Zoom Telehealth in order to rule out exclusionary criteria and confirm inclusion criteria. Furthermore, consent and assent forms will be sent to participants’ caregivers prior to their in-person visit to read and review. The in-person consent process will occur at the visit to local Children’s Hospital.

Study staff will obtain written consent from at least one of the participant’s caregivers, and participants will be asked to read and sign or “make their mark” on an assent form. These participants will be asked specific structured questions after the study staff reviews the consent document with them, but before consenting, to ensure they have sufficient understanding to consent to the study (e.g., “what are some of things you will be asked to do in this study?” “how would you tell us if you wanted to stop being in this study?” “what are the risks of this study?”). Participants will receive a verbal explanation of the purposes, procedures, and potential risks of the study and of their rights as research participants. They will also be given the opportunity to discuss the study with caregivers prior to agreeing to participate. If it is determined that these participants cannot provide assent, they will be excluded from the study.

The investigator will explain the research study to the participant and their caregiver, and answer any questions that may arise. Researchers will emphasize to both participants and their caregivers that they retain the right to withdraw consent at any time throughout the course of the study, and that their comfort and safety is a priority. A copy of the informed consent document(s) will be given to the participant and their caregiver for their records.

After consenting at the study visit, participants will complete three research-based cognitive–motor tasks in a virtual reality environment while connected to fNIRS optodes. As previously mentioned, other participants and their caregivers will also complete a variety of questionnaires and assessments that are a part of the larger, long-term work beyond the scope of this current paper (Table S2). Further cognitive and neural outcomes, beyond those that are feasibility related, will also be evaluated (Table S1). In the following description of the methods and results, we focus on the preliminary, feasibility-based outcomes central to this paper. This protocol has been reviewed and approved by the Institutional Review Board of Children’s National Research Institute (Protocol Number: STUDY00001552).

### 2.2. Participants

This work will assess 50 autistic children and 50 non-autistic children. We anticipate having to screen a higher number of participants to accommodate ineligibility. We estimate that we will lose 10% of participants at screenings, 20% of screened participants will choose not to enroll, and 10% of participants will dropout after enrollment. Given these factors, we estimate needing to screen at least 160 participants.

All participants will be between the ages of 8 and 12 years old. This age range corresponds with the “context-specific” period of motor development, marking the transition children make from executing basic movements to incorporating these skills within more complex settings requiring cognitive and motor skills [1]. Conducting this feasibility study within this narrow yet significant age range will set the foundation for future work examining how and why autistic children might differ in their cognitive and motor abilities compared to their non-autistic peers, as well as whether these differences correspond with their engagement in complex cognitive–motor individual and group activities.

Participants will be recruited via a database in collaboration with a local children’s hospital. Eligible youth must be right-handed, between the ages of 8 and 12 years old at the time of study enrollment (inclusive), and willing to participate in the study. Child participants must be able to follow directions and answer questions as needed, with an IQ (either previously assessed within the past two years, or assessed via The Wechsler Abbreviated Scale of Intelligence—2nd Edition (WASI-II; Wechsler, 2011) during the study visit) of 70 [51]. Both the child and accompanying parent must speak English well enough to complete consent and study procedures as our staff are unable to provide assessments in any other language besides English. Autistic participants must have a prior diagnosis within the past two years and will be confirmed via the Autism Diagnostic Observation Schedule—2nd edition (ADOS-2). Participants without a clinical diagnosis should provide staff with detailed developmental history including early childhood milestones and behavior patterns. Participants will then be able to complete the ADOS-2 to receive a diagnosis. The ADOS-2 will be administered by a licensed clinical psychologist who has been previously trained in administration with a minimum of 80% inter-rater reliability. The specific modules used will depend on each participant’s level of expressive language. Non-autistic participants will be confirmed to have no autism diagnosis as well as no first-degree relatives with an autism diagnosis.

Both autistic and non-autistic participants will be excluded due to: the usage of any psychiatric or neurologic medications that may affect study participation or the resulting neuroimaging data (e.g., substances affecting neurovascular coupling, including (but not limited to) certain psychostimulants [52] or antidepressants [53]; the presence of skin lesions or conditions on the head which may prevent proper application of fNIRS optodes; known developmental and intellectual disabilities, medical disabilities, or disorders (aside from autism) which would interfere with study participation (e.g., cerebral palsy, epilepsy); and uncorrected visual impairment, colorblindness, and/or deafness. Participants may also be excluded due to a BMI in the obese range which may prevent participation in fNIRS data collection [54].

### 2.3. Materials and Equipment

We will use the Meta Quest Pro Virtual Reality Headset (Meta Platforms, Inc., Menlo Park, CA, USA; released 2022) and Touch Controllers (Meta Platforms, Inc., Menlo Park, CA, USA) to collect kinematic data. All the VR task development and code will be written using Unity (Version 6000.4.7f1, Unity Technologies, San Francisco, CA, USA), and all the tasks are designed to be fully immersive. The tasks will be designed for use by right-handed individuals specifically. The Meta Quest Pro is a standalone headset with integrated eye and face tracking via 10 onboard sensors, dual LCD displays at 1800 × 1920 pixels per eye, and a 106° × 96° field of view. The controller sampling rate is 1000 Hz, and the Unity frame Refresh Rate is 90 Hz. Our neuroimaging method will involve use of the NIRScout fNIRS system (NIRx Medical Technologies, Glen Head, NY, USA) and the NIRStar (v15.3) data acquisition software, sampling at a rate of 10 Hz. Figure 1 depicts the full experimental setup, with specific materials and their specifications highlighted in Figure 2.

#### fNIRS Montage Design

The fNIRS probe design follows the 10/10 electrode placement system and will be designed in NIRSite (Version 2023.9; NIRx Medical Technologies, Berlin, Germany). The design, while relatively limited due to the placement of the VR headset, will involve 8 sources and 8 detectors (20 channels), centered bilaterally across frontal and motor areas. The interoptode distance will remain standard (30 mm). Figure 3 below depicts a proposed montage, designed in NIRSite, with channels overlying these brain regions of interest.

### 2.4. Data Synchronization

Synchronization between VR events and fNIRS data will be achieved using Lab Streaming Layer (LSL), a technique commonly used for temporal synchronization in multimodal research [55]. First, during the initialization of the VR task, the headset will open a TCP/UDP socket to a relay laptop on the same local network, establishing a connection to a relay laptop via a custom Python (v3.13.15) code. The relay laptop, running a Python LSL script, then accepts the connection from the headset and ultimately creates an outlet for VR event markers and an inlet to receive fNIRS data. The Python script locates the fNIRS data stream and continuously pulls the samples with precise timestamps of triggered events, such as task start and user response times. These events are sent from the VR headset to the relay laptop, with their corresponding time stamps marked in the fNIRS time domain.

To note, LSL uses a network time protocol (NTP)-inspired clock offset measurement technique to measure the difference between the outlet and inlet clocks and adjust the delay. This correction is done periodically and utilizes a recursive least squares filter to reduce jitter effects. This allows the VR events and fNIRS measurements to be aligned within millisecond-level accuracy to streamline further data analysis.

### 2.5. Research-Based Task Design and Protocol Overview

Our cognitive–motor research-based task involves three variations of a balloon popping task, adapted from a bubble popping task used in Minissi et al., 2023 [34]. These require participants to reach and click, or “pop,” a series of balloons via their VR controller. The balloons presented as targets for participants vary in color according to the task. Conceptually, the “balloon-popping” concept was designed around the foundation of Fitts’s Law, which emphasizes a speed/accuracy tradeoff while reaching between targets [56]. In the motor control and performance literature that incorporates Fitts’s Law into the task design, the difficulty of target-reaching tasks is often manipulated by changing the size of the targets themselves or the distance between them. For the sake of relative simplicity in our study design, we chose to keep the motor difficulty constant across our task conditions—the size of the balloons remains the same throughout, and the initial “target” is the participant’s “reset” position, where they bring their hand to rest under their chin after each trial.

To manipulate cognitive difficulty of the balloon popping tasks, we incorporated the “Go/No-Go” paradigm by changing the color of the balloons presented to participants and asking them to only pop certain colors. The traditional Go/No-Go paradigm is designed to test response inhibition—for example, a participant may be asked to refrain from responding to a stimulus of a particular color. We incorporated this paradigm to manipulate the cognitive difficulty of our balloon-popping task across three conditions: Go/No-Go, Reach-and-Pop, and Go/No-Go Reach-and-Pop. For example, in the Go/No-Go condition, participants must only pop purple balloons when they appear, ignoring all other balloon colors presented. Respectively, the Go/No-Go, Reach-and-Pop, and Go/No-Go Reach-and-Pop tasks are intended to measure cognitive, motor, and cognitive–motor domains. We will assess a small selection of cognitive outcomes of the Go/No-Go task, including commission errors (i.e., an erroneous response to a No-Go signal during a Go/No-Go trial) and omission errors (i.e., the failure to respond to a Go signal during a Go/No-Go trial). See Table 1 for full descriptions of each task condition and their respective cognitive and motor outcomes, Figure 4 for visual depictions of each task condition, and Figure 5 for a detailed breakdown of the timestamps embedded in the experimental block design. Table 1 also mentions the brain regions of interest for these tasks: the motor cortex for movement purposes, and the prefrontal cortex/dorsolateral prefrontal cortex for executive function purposes. fNIRS studies assessing movement [57] and those evaluating Go/No-Go performance [58] typically assess these brain regions.

### 2.6. Block Design and Task Details

The “Go/No-Go” paradigm is embedded within a block design, a common experimental design among fNIRS studies, which traditionally alternates task periods, or blocks, with periods of rest. There will be two experimental conditions: cognitive, and motor/cognitive–motor. The cognitive condition will consist of 6 block sets, with each task block (either go or Go/No-Go blocks) running for 24 s. Each task block will also be preceded by 3 s of brief instructions (e.g., “Press the button to pop the balloons”). Therefore, one block set (two 24 s blocks, with two sets of 3 s instructions) will total 54 s, with 6 consecutive block sets totaling 5.4 min (or 324 s). Prior to the condition, there will also be a 15 s calibration period for the headset and controllers, totaling 339 s (5.65 min) for the cognitive condition. The motor/cognitive–motor condition will consist of 12 block sets, with each task block (either go or Go/No-Go blocks) running for 24 s. Each task block will also be preceded by 3 s of brief instructions (e.g., “Press the button to pop the balloons. Be as fast and as accurate as you can.”). Therefore, one block set (two 24 s blocks, with two sets of 3 s instructions) will total 54 s, with 12 consecutive block sets totaling 10.8 min (or 648 s). Prior to the condition, there will also be a 15 s calibration period for the headset and controllers, totaling 663 s (11.05 min) for the motor/cognitive–motor condition. To mitigate possible carry-over effects between conditions, participants will be allotted up to five minutes to rest between the two conditions, and the order in which the conditions are presented will be counterbalanced across participants.

During the cognitive condition, each balloon stimulus will be displayed sequentially for 800 milliseconds, with an inter-stimulus interval of 200 milliseconds. In the motor/cognitive–motor condition, each balloon stimulus will be displayed for 3200 milliseconds, with an inter-stimulus interval of 800 ms. The balloons will be light blue and dark purple in the cognitive condition, and dark blue or light purple in the motor/cognitive–motor condition—in both conditions, participants will be asked to pop the purple balloons. Shades of blue and purple were specifically chosen for both conditions to control for the effect of color wavelengths on accuracy. Research has shown that shorter color wavelengths (i.e., blues and purples) are associated with higher accuracy in VR Go/No-go tasks [59]—therefore, it is plausible that including balloon color combinations with longer wavelengths in one condition versus another could have detrimental effects on accuracy that are unrelated to the nature of the condition itself. The order in which these colors appear throughout each block will be randomized for each participant, and the Go/No-Go ratio will be 50% (i.e., participants will need to respond to half the stimuli presented and inhibit their response to the other half). The locations of the stimuli will remain the same for each trial in order to control for the potential effect of randomized locations on kinematic measures.

The timing of the block design in each condition was largely based on the protocol used in a study that used fNIRS to assess Go/No-Go task performance among children with ADHD [60]. Similar to that study, our block design does not include rest periods between blocks—only one break between the two conditions—so as to not bore participants or lose their focus [60]. Furthermore, the go blocks in each condition are considered the baseline, rather than rest blocks. The study that the current design is based on suggests that, since brain activation during the Go/No-Go blocks is reflective of inhibitory control, it is more appropriate for the go blocks to be the baseline comparison, rather than rest blocks [60]. The block design timing was only altered for the motor/cognitive–motor condition to account for movement time from the hand to the balloon.

### 2.7. Participant Procedures and Instructions

Prior to each condition, each subject will perform one practice block to ensure their understanding of the task. Verbal assistance and clarification will be provided during the practice block as needed. The entire time allotted for the practice block will not exceed the total cognitive condition time (i.e., 5.65 min). If, after the maximum time allotted for practice, the participant still does not understand the task, the data collection session will be discontinued. The following instructions will be used prior the go and Go/No-Go blocks in each condition:Go Block Instructions (Cognitive Condition): “Press the button to pop the balloons. Be as fast and as accurate as you can.”Go/No-Go Block Instructions (Cognitive Condition): “Do not pop the blue balloons. Be as fast and as accurate as you can.”Go Block Instructions (Motor Condition): “Reach for the balloons and press the button to pop them. Be as fast and as accurate as you can.”Go/No-Go Block Instructions (Cognitive–Motor Condition): “Reach for the balloons, and press the button to pop them. “Do not pop the blue balloons. Be as fast and as accurate as you can.”

During the practice block, the instruction display will not have a time limit. During the actual conditions, and given that the participant is familiar with the instructions at that point in the experiment, the appropriate instructions will be displayed for 3 s prior to each block.

Signal optimization for each channel will be obtained by proper cap fit, as well as moving participants’ hair underneath optodes as needed for the near-infrared light to properly reach the scalp. This process is non-invasive and will take approximately 15 min to set up before the start of the fNIRS recording.

Throughout set-up and the research-based tasks, researchers will remain attentive to study participant fatigue and discomfort and will check in regularly to assess their comfort. If needed, researchers will adjust the length of the test sessions to each individual (e.g., a longer break between the two conditions, two testing sessions, etc.) accordingly. Furthermore, researchers will continuously emphasize that participation is voluntary and that comfort is a priority—they will immediately stop testing upon participants’ requests. Should the subject report any significant discomfort, the procedure will be immediately terminated. No clinical decisions will be based on the results of fNIRS and VR as they are both solely research paradigms.

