**Abstract:**

**Background/Objectives**: In both typical and atypical development, there is growing evidence that motor development sets the stage for development in other domains. This study aims to examine the feasibility of conducting cognitive and motor research-based tasks in a virtual reality (VR) environment with concurrent neuroimaging (functional near-infrared spectroscopy, or fNIRS) in autistic children. **Methods**: During a single study visit, participants will complete research-based tasks conducted in a virtual reality environment while wearing the fNIRS apparatus. Supplementary procedures will include a range of standardized assessments and questionnaires for caregivers and their children to complete. **Anticipated Outcomes**: These methods will yield a rich combination of data -- the kinematic data associated with performance during the research-based tasks, as well as the neural correlates underlying this performance. **Conclusions**: The overarching, long-term goal of this feasibility study is to explore the interrelationships between cognitive, motor, and social development in autistic children using a variety of research methodologies. A better understanding of these relationships and their neural correlates will inform future research, assessment methods, and intervention strategies across the autism spectrum.

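### Failing practice for one condition ends the whole session, so a child who would fail only one practice supplies the other condition's task measures in one order but not in the other

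*Protocol article*

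**What the plan says.** Section 2.6: "There will be two experimental conditions: cognitive, and motor/cognitive–motor". The second condition holds both the motor (go) blocks and the cognitive–motor (Go/No-Go) blocks. To limit carry-over, "the order in which the conditions are presented will be counterbalanced across participants".

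Section 2.7: "Prior to each condition, each subject will perform one practice block to ensure their understanding of the task". Practice is capped at 5.65 minutes. If, after that, "the participant still does not understand the task, the data collection session will be discontinued". The test of understanding is specific to a condition; the consequence is stated for the session.

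Two passages bear on what the session means. The Abstract plans one visit: "During a single study visit, participants will complete research-based tasks conducted in a virtual reality environment while wearing the fNIRS apparatus". Section 2.7 also says, in its text on fatigue and discomfort, that where this is called for "researchers will adjust the length of the test sessions to each individual (e.g., a longer break between the two conditions, two testing sessions, etc". Nothing provides for moving on to the other condition after a failed practice.

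The Measures paragraph under Aims and Hypotheses and Table 2 list task-specific behavioural measures and fNIRS quality as primary. Table 1 sets these out by task. Section 2.2 plans that "10% of participants will dropout after enrollment".

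**The concern.** Consider a child who can do the button-press task but cannot follow the reaching task. With the cognitive condition first, commission errors and an fNIRS recording are obtained before the session stops at the second practice. With the motor/cognitive–motor condition first, the session stops at once and nothing is recorded. The child's ability is the same; only the assigned order differs.

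The stated primary aim covers both cognitive and motor tasks, so it matters how many children can supply data on each. Under the written rule, the set of children with data in one condition depends partly on their understanding of the other, and only in one of the two orders. That set is then no longer balanced on order. Data that were never collected cannot be restored in analysis.

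**Working it through.** **The plan's own figures.** One block set is 2 × (24 + 3) = 54 s. The cognitive condition is 6 × 54 + 15 = 339 s = 5.65 min, which matches the stated practice cap. The motor/cognitive–motor condition is 12 × 54 + 15 = 663 s = 11.05 min, also as stated.

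**Inputs.**
- Two conditions in counterbalanced order, so about half of the children per order (section 2.6).
- 50 children per group (section 2.2), used here as a round base of children starting practice; 25 per order.
- Practice failure rates pC (cognitive) and pM (motor/cognitive–motor). The article gives neither, so the values below are assumptions, taken not to change with order.
- Data recorded before a stop are kept (assumption; the text says only that the session stops).

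**Formulas.** Cognitive data exist with probability 1 − pC when that condition is first, and P(pass both) when it is second. If only the failed condition were stopped, they would exist with probability 1 − pC in both orders. The loss averaged over orders is therefore

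loss (cognitive) = ½ × P(pass cognitive, fail motor),

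and symmetrically for motor. Under independence:
- loss (cognitive) = ½ × pM(1 − pC)
- loss (motor) = ½ × pC(1 − pM)

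**Case within the planned dropout: pC = pM = 5%, independent.**
- Failing at least one practice: 1 − 0.95² = 9.75%.
- Availability per condition: (0.95 + 0.9025)/2 = 92.6%, instead of 95%.
- Loss: 0.02375 × 50 = 1.2 children per group, per condition.
- Order balance among children with cognitive data: 25 × 0.95 = 23.75 (cognitive first) against 25 × 0.9025 = 22.56 (motor first).
- Completing both conditions: 25 × 0.9025 = 22.56 in either order.

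**Range.** Each availability cell gives the value under the written rule, then the value if only the failed condition were stopped.

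| pC, pM | Dependence | Fail at least one | Cognitive available | Motor available | Lost per 50 (cognitive; motor) |
|---|---|---|---|---|---|
| 2%, 5% | independent | 6.9% | 95.55%; 98% | 94.05%; 95% | 1.2; 0.5 |
| 5%, 5% | independent | 9.75% | 92.6%; 95% | 92.6%; 95% | 1.2; 1.2 |
| 5%, 10% | independent | 14.5% | 90.25%; 95% | 87.75%; 90% | 2.4; 1.1 |
| 10%, 20% | independent | 28% | 81%; 90% | 76%; 80% | 4.5; 2.0 |
| 5%, 5% | same children fail both | 5% | 95%; 95% | 95%; 95% | 0; 0 |
| 10%, 20% | cognitive failures nested in motor failures | 20% | 85%; 90% | 80%; 80% | 2.5; 0 |

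The 5%/10% and 10%/20% rows put more children into practice failure than the 10% that section 2.2 allows for all dropout. If at most 10% fail any practice, P(fail only the other) is at most 10%, so the loss in one condition is at most 5 points, or 2.5 children per 50.

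**The case against.** The strongest reply concerns consequence. A reader might infer that the rule makes the headline feasibility result depend on order, or makes a feasible task look infeasible. The documents do not support that. Hypothesis 1 and Table 2 count participants who complete all assessments and tasks. Under these assumptions that share is (1 − pC)(1 − pM) in either order. The article sets no completion threshold per task, and section 3 describes the results as descriptive and qualitative. This stands: the effect is confined to the per-condition measures, their denominators and their order balance.

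Second, the loss may be very small. The cognitive–motor task reuses the purple/blue rule, so a child who cannot grasp that rule would probably fail both practices, and then order costs nothing. Eligibility requires the ability to follow directions and includes an IQ criterion. Practice comes with verbal help and untimed instructions. This also stands. It limits the size but does not remove the mechanism, because reaching and returning the hand to the start position are demands of one condition only.

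Third, the session might mean one condition's run. The text does not say so. The single visit points to the whole session, and the possible second session is offered for fatigue and discomfort. If one condition was meant, the same sentence needs clarifying.

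Fourth, section 3.1 applies the channel criterion per participant. That is so, but Table 1 lists signal quality under the cognitive and motor tasks, and a child stopped at the first practice has no task recording to which the criterion could be applied.

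Finally, it is tempting to add that no rule says how an unattempted condition is scored. An article may leave that to the full protocol or analysis plan, so it is not part of this point.

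**Conclusion.** The point holds as a modest, avoidable loss of data. Read together, sections 2.6 and 2.7 mean that a child who would fail exactly one practice supplies the other condition's primary task measures in one order only, and nothing elsewhere in the article repairs this. The size is half the probability of failing only the other practice. With independent failures at 5% each, that is about 2.4 percentage points, or 1.2 children per group of 50 in each condition, and it falls toward zero as failures cluster in the same children. Larger figures need failure rates above the whole planned dropout. The link between practice failure and that 10% is itself an inference, since the article does not say what the dropout consists of. The overall completion count is unaffected by order. This is a cheap improvement to the design and does not threaten the study's main conclusion.

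**What to change.** In section 2.7, state that failing practice ends only the condition concerned, and that the other condition, with its own practice, is then offered to a child who is willing. Leave the discomfort and voluntary-stop rules in the same section unchanged. Record completion and comprehension failure separately for each condition, and keep completion of all tasks as the overall Hypothesis 1 figure. This brings the order-dependent loss to zero and keeps a useful feasibility result: which task a child could not understand.

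The cost is one sentence and one field per condition. A few children would spend up to one further practice and condition at the visit: at most 5.65 + 5.65 = 11.30 min if the cognitive condition remains, or 5.65 + 11.05 = 16.70 min if the motor/cognitive–motor condition remains, plus any rest between conditions. The plan already allows that time for a child who passes the first practice.

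### The two Go/No-Go scripts fixed in Section 2.7 do not match the task rule: one gives no instruction to respond, and the other does not forbid reaching for blue

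*Protocol article*

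**What the plan says.** The task rule is stated in several places and is consistent. Section 2.5 says of the Go/No-Go condition that "participants must only pop purple balloons when they appear, ignoring all other balloon colors presented". Section 2.6 says "in both conditions, participants will be asked to pop the purple balloons", and sets a 50% ratio under which "participants will need to respond to half the stimuli presented and inhibit their response to the other half". Table 1 names purple balloons as the targets and says that blue ones are to be left alone. The legend to Figure 4C adds that on a No-Go trial of the cognitive–motor task the child neither reaches for nor pops the balloon.

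Section 2.7 then prints four scripts as fixed text: "The following instructions will be used prior the go and Go/No-Go blocks in each condition". During the conditions, "the appropriate instructions will be displayed for 3 s prior to each block".

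- Cognitive, go: press the button to pop the balloons, then the speed and accuracy sentence.
- Cognitive, Go/No-Go: "Do not pop the blue balloons. Be as fast and as accurate as you can".
- Motor, go: "Reach for the balloons and press the button to pop them", then the speed and accuracy sentence.
- Cognitive–motor, Go/No-Go: nearly the same reach-and-press sentence, then the ban on popping blue, then the speed and accuracy sentence.

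Section 2.6 and the legend to Figure 5 illustrate the instructions for the motor/cognitive–motor condition with "Press the button to pop the balloons. Be as fast and as accurate as you can". That is the cognitive go script and does not mention reaching.

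**The concern.** The scripts are part of the standardized stimulus, because they are shown before every block. They depart from the task rule in two ways.

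1. The cognitive Go/No-Go script has one explicit rule, a prohibition. It is the only one of the four without an instruction to respond. Its cognitive–motor counterpart asks the child both to respond and to withhold, so the two tasks differ in instruction as well as in movement.
2. The cognitive–motor script says to reach for the balloons without restriction and bars only the pop for blue. A child who reaches for a blue balloon and does not press has followed the script but broken the rule in Figure 4C.

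Commission errors are a primary feasibility-based outcome for both tasks in Table 1 and the only cognitive outcome in Table 2. Section 2.6 also takes the go blocks as the baseline for the Go/No-Go blocks, so wording that changes between them sits inside the contrast meant to reflect inhibition.

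**Working it through.** **Timing and exposure.** Inputs from Section 2.6: two 24 s blocks per set, 3 s of instructions before each block, 15 s calibration, 6 sets (cognitive) or 12 sets (motor/cognitive–motor).

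- Cognitive: 6 × 2 × (24 + 3) = 324 s; 324 + 15 = 339 s = 5.65 min. This matches the plan.
- Motor/cognitive–motor: 12 × 2 × (24 + 3) = 648 s; 648 + 15 = 663 s = 11.05 min. This also matches.

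The next figures assume that each set holds one go and one Go/No-Go block, as the design implies, and that the nominal stimulus timing is kept.

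- Cognitive: 24 / (0.8 + 0.2) = 24 balloons per block; 6 × 24 = 144 in Go/No-Go blocks, so 72 Go and 72 No-Go.
- Cognitive–motor: 24 / (3.2 + 0.8) = 6 balloons per block; 12 × 6 = 72, so 36 Go and 36 No-Go.

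**Scripts against rule.**

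| Go/No-Go script | Tells child to respond? | Names purple? | Bars pop of blue? | Bars reach for blue? |
|---|---|---|---|---|
| Cognitive | No | No | Yes | Not applicable |
| Cognitive–motor | Yes | No | Yes | No |
| Task rule | Yes | Yes | Yes | Yes (Figure 4C, cognitive–motor) |

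**Baseline against comparison.** In the motor/cognitive–motor condition, the Go/No-Go script is in substance the go script plus a prohibition, so the wording changes only by what the contrast is meant to add. In the cognitive condition, the go script says to press, and the Go/No-Go script drops that instruction as well as adding the prohibition.

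**What the listed outcome can show.** As a limiting case, a child who never pressed in the cognitive Go/No-Go blocks would have 0/72 commission errors, 72/72 omission errors and 72/144 = 50% overall accuracy. Section 2.5 names omission errors as an outcome to be assessed, but Tables 1 and 2 do not list them. Commission errors read alone would not separate good inhibition from reduced responding. This shows why the emphasis of the script matters for that outcome. It does not predict how children will behave.

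**The case against.** The strongest reply is that the on-screen text is only a reminder. Section 2.7 gives each child a practice block before each condition, with verbal clarification and no time limit on the instruction display, and discontinues the session if the child still does not understand. The go-block script says to press. Section 2.6 uses only two colors per condition, so a child told to leave blue alone can work out that purple is the target. Asking for speed makes little sense unless a response is expected. All of this stands, and it makes the practical risk small. It does not reconcile the printed scripts with the rule, and verbal clarification given as needed can vary between children where the printed script does not.

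Four stronger readings are tempting, and the documents do not support them.

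- *A child who presses nothing has obeyed the script, so non-responding should be expected.* This takes the prohibition alone and overlooks the safeguards above. Omission errors, if assessed as Section 2.5 says, would also expose such a child.
- *A difference in commission errors between the tasks would reflect wording.* Section 3 describes feasibility results as descriptive and qualitative, and no test between the tasks is described. The tasks also differ in display time (800 against 3200 ms), interval (200 against 800 ms), color shades and reaching.
- *Kinematic trials would be lost because the example in Section 2.6 omits the reach.* That text is marked as an example, and Section 2.7 gives the operative reaching scripts.
- *All four scripts are defective because none names purple.* The go scripts need no color word: Table 1 describes the Reach-and-Pop balloons as being of one color, and the go blocks call for no choice between colors.

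**Conclusion.** The point holds as a mismatch between the two fixed Go/No-Go scripts and the task rule. The cognitive script lacks the instruction to respond, the cognitive–motor script does not bar reaching for blue, and neither names the target color. Instruction emphasis therefore differs between the two tasks and, in the cognitive condition, between the go baseline and the Go/No-Go blocks. It affects the script before 6 cognitive and 12 cognitive–motor Go/No-Go blocks, on the pairing assumed above.

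The effect on commission errors cannot be sized from the documents. Any percentage would only restate the assumption put in. It is worth correcting before first use because it touches a listed primary outcome and is nearly free to change. It does not threaten the study.

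**What to change.** Reword the two Go/No-Go scripts in parallel and leave the two go scripts as they are. For example, each followed by the existing speed and accuracy sentence:

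- Cognitive: *Press the button to pop the purple balloons. Do not pop the blue balloons.*
- Cognitive–motor: *Reach for the purple balloons and press the button to pop them. Do not reach for or pop the blue balloons.*

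As a minor consistency edit, replace the button-only example for the motor/cognitive–motor condition in Section 2.6 and the Figure 5 legend with a reaching script from Section 2.7.

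Cost: two text strings in the task code and two example sentences. With the speed and accuracy sentence (9 words), the cognitive script grows from 6 + 9 = 15 to 8 + 6 + 9 = 23 words, still below the present cognitive–motor script at 11 + 6 + 9 = 26. The cognitive–motor script grows from 26 to 12 + 9 + 9 = 30. The downside is slightly more to read in a 3 s display, for children who will already have seen the text without a time limit in practice.
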